**Secondary outcomes — Glycaemic control**			
Postoperative hyperglycaemia incidence	Proportion of participants with any blood glucose ≥180 mg/dL during POD 0–5, stratified by baseline diabetes status	POD 0–5	Chi-square or Fisher’s exact test; logistic regression adjusting for diabetes
Insulin requirement	Total insulin units administered during POD 0–5	POD 0–5	Two-sample t-test or Wilcoxon rank-sum test

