**Caloric target and dose calculation.** The daily caloric target during the intervention period is set at 20 kcal/kg/day, in keeping with current evidence supporting permissive hypocaloric feeding to avoid perioperative overfeeding. Body weight used for dose calculation is determined by body mass index (BMI): actual body weight is used for participants with BMI < 25 kg/m², and ideal body weight—calculated as height (m)² × 23 (a reference body-mass index of 23 kg/m², consistent with recommendations for Asian populations) [21], applied to both sexes—is used for those with BMI ≥ 25 kg/m². The required daily PN volume is back-calculated from the caloric target using the energy density of the assigned product (0.69 kcal/mL for the control and 0.67 kcal/mL for the investigational product), rounded to the nearest 1 mL, and delivered through a volumetric infusion pump. The calculated daily volume is not expected to exceed the manufacturer-stated maximum of 40 mL/kg/day. For a 75-kg participant, the control formulation delivers approximately 68 g of amino acid per day (0.9 g/kg) and the high-protein formulation approximately 84 g (1.1 g/kg); detailed examples are provided in S2 and S3 Tables. These amino-acid amounts represent PN-only delivery; the total protein supply (oral plus parenteral) that forms the basis of the nitrogen-balance calculation is higher, and the between-arm difference should be interpreted as a difference in PN-delivered rather than total protein.

**Stepwise PN delivery schedule.** PN is administered through a peripheral intravenous line; central venous access is not required. Peripheral access was chosen to avoid the infection and thrombosis risks of central venous catheterisation, consistent with the broader Enhanced Recovery After Surgery (ERAS) principle of minimizing invasive perioperative procedures. PN is initiated on the preoperative day (preoperative day −1; POD −1), withheld on the day of surgery (POD 0) because of perioperative anaesthetic and surgical considerations, and resumed from POD 1 through POD 5, for a total of six administration days. The PN dose on each day is delivered as a fixed proportion of the daily caloric target, decreasing stepwise as anticipated oral intake advances: 80% on POD −1, 100% on POD 1, 60% on POD 2 and POD 3, and 50% on POD 4 and POD 5. The stepwise schedule is summarized in Table 3.

**Table 3 pone.0355677.t003:** Stepwise perioperative parenteral nutrition delivery schedule.

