**Monitoring and dose modification.** During the intervention period, blood glucose, serum electrolytes, hepatic and renal function tests, body weight, and urine output are monitored daily by the NST. The assigned PN may be temporarily withheld or reduced at the investigator’s discretion for predefined safety triggers, including blood glucose ≥250 mg/dL, clinically significant hepatic enzyme elevation, or mild to moderate infusion-site reactions. Permanent discontinuation of the allocated PN with withdrawal from the per-protocol population is reserved for severe intra- or postoperative complications — including anastomotic leak, bacteremia, or fungemia — and for severe infusion-related events that preclude further PN (e.g., refractory infusion-site pain or phlebitis); in such cases the allocated PN is discontinued at the discretion of the treating clinician, and the participant is retained in the intention-to-treat population and flagged for sensitivity analysis. Any modification or discontinuation of the assigned regimen, together with the reason, is documented on the case report form. Adherence to the allocated intervention is summarized as the proportion of planned PN doses received and the cumulative volume of allocated PN administered during POD −1 through POD 5.

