**Secondary outcomes — nutritional status.** Secondary nutritional outcomes include the skeletal muscle index measured at the third lumbar vertebral level on abdominopelvic computed tomography; composite nutritional and inflammatory–nutritional indices comprising the Nutritional Risk Screening 2002 (NRS-2002), GLIM criteria, Prognostic Nutritional Index (PNI), C-reactive protein–to-albumin ratio (CAR), and modified Glasgow Prognostic Score (mGPS); serum nutritional biomarkers (albumin, prealbumin, total protein); and longitudinal changes in body weight, body composition assessed by multifrequency segmental bioelectrical impedance analysis (InBody 770; InBody Co., Ltd., Seoul, Republic of Korea), and handgrip strength assessed by hand dynamometry.

**Secondary outcomes — glycemic control.** Postoperative glycemic outcomes comprise the proportion of participants with any blood glucose ≥180 mg/dL during POD 0 through POD 5, stratified by baseline diabetes status, together with the cumulative insulin requirement during the same period. Because the investigational formulation also delivers less carbohydrate, these glycemic outcomes partly reflect the compositional difference in carbohydrate load and are interpreted accordingly.

**Secondary outcomes — postoperative complications.** Postoperative complications occurring within 30 days after surgery are classified using the Clavien–Dindo classification. Specific complications captured include surgical site infection; pneumonia; delayed gastric emptying; and anastomotic leak.

**Secondary outcomes — functional recovery.** Functional recovery milestones aligned with the institutional ERAS pathway include time to first defecation, time to tolerate ≥50% of a soft diet for 24 hours, time to independent corridor ambulation, and length of postoperative hospital stay. Patient-reported recovery outcomes are assessed at POD 14, 1 month, 3 months, 6 months, and 12 months, and encompass oral intake (proportion relative to preoperative volume and meal frequency), early satiety, appetite loss, gastrointestinal symptoms (nausea, vomiting, dumping, reflux, diarrhoea, constipation), oral nutritional supplement use, and habitual physical activity. Clinical events—including emergency department visits, readmissions, and interventions—are captured through 12 months.

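### The any-hyperglycaemia outcome over POD 0–5 pools the surgery day, when PN is withheld, with the PN days, which dilutes the between-arm contrast (minor, exploratory outcome)

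*Protocol article*

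**What the plan says.** Table 4 (Secondary outcomes — Glycaemic control) defines the hyperglycaemia outcome as "Proportion of participants with any blood glucose ≥180 mg/dL during POD 0–5, stratified by baseline diabetes status", compared by a chi-square or Fisher test and by logistic regression adjusting for diabetes. The companion outcome is "Total insulin units administered during POD 0–5". The Outcomes section uses the same window and names its purpose: "Postoperative glycemic outcomes comprise the proportion of participants with any blood glucose ≥180 mg/dL during POD 0 through POD 5". It adds that, since the investigational product carries less carbohydrate, "these glycemic outcomes partly reflect the compositional difference in carbohydrate load and are interpreted accordingly".

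Under Interventions (Stepwise PN delivery schedule, and Table 3), PN starts on POD −1, is "withheld on the day of surgery (POD 0) because of perioperative anaesthetic and surgical considerations, and resumed from POD 1 through POD 5". Coverage of the daily caloric target is "80% on POD −1, 100% on POD 1, 60% on POD 2 and POD 3, and 50% on POD 4 and POD 5".

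The Monitoring and dose modification paragraph says that during the intervention period "blood glucose, serum electrolytes, hepatic and renal function tests, body weight, and urine output are monitored daily by the NST". Table 4 also lists glucose among the laboratory safety values, with a between-group comparison at each timepoint, POD −1 included. The notes to Table 4 and the Statistical analysis section class the glycaemic outcomes as exploratory, reported with 95% confidence intervals and without multiplicity adjustment.

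**The concern.** The window joins one day on which neither arm receives trial PN to five days on which both do. Under an *any* rule the first event settles the participant's status. A patient with 210 mg/dL on the day of surgery and every later value below 180 mg/dL counts the same as a patient who first exceeds the threshold on full-dose PN on POD 1. If surgery-day hyperglycaemia is about equally common in both arms, those participants become events whatever the formulation later does, and the contrast narrows.

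What is at stake is the reading of an exploratory comparison. The protocol intends to read these outcomes partly in the light of the difference in carbohydrate load. That difference is small, so there is little signal to lose, and a null POD 0–5 result would be hard to interpret.

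**Working it through.** **1. Window against exposure.** Coverage from the stepwise schedule, in per cent of a daily target:

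| Day | POD −1 | POD 0 | POD 1 | POD 2 | POD 3 | POD 4 | POD 5 |
|---|---|---|---|---|---|---|---|
| PN coverage | 80 | 0 | 100 | 60 | 60 | 50 | 50 |
| In outcome window | no | yes | yes | yes | yes | yes | yes |

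The total is 400, that is 4.0 full-dose days. As a check, this total reproduces the plan's own cumulative nitrogen difference of roughly 8 g: (20/0.67 × 6.17 − 20/0.69 × 5.21) mg/kg = 33.2 mg/kg per full-dose day; × 4.0 × an assumed 60 kg = 8.0 g. POD 1–5 carries 320/400 = 80% of scheduled PN. POD 0–5 also carries 80%, because POD 0 adds nothing.

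**2. Size of the carbohydrate contrast.** From the glucose content in Table 2 and the energy densities at 20 kcal/kg/day: control 20/0.69 × 70.7 mg = 2.05 g/kg/day; investigational 20/0.67 × 64.4 mg = 1.92 g/kg/day. The difference is 0.127 g/kg/day, or 6.2%, at full coverage.

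**3. Dilution under the *any* rule.** Let q be the POD 0 event risk, equal in both arms, and p the POD 1–5 risk in an arm. Then

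P(any POD 0–5) = q + P(no event on POD 0 and an event on POD 1–5).

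The q cancels between arms. With independent days the second term is (1 − q)p, so

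RD(POD 0–5) = (1 − q) × RD(POD 1–5).

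With positive correlation, the participants who would have events on POD 1–5 are more often already events on POD 0, and the difference shrinks further.

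The documents give no glycaemic event rates, so the inputs here are assumptions: p = 35% and 25% (difference 10 points), and a latent normal correlation of 0 or 0.5 between POD 0 and POD 1–5.

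| POD 0 risk q | RD, independent | RD, correlation 0.5 |
|---|---|---|
| 10% | 9.0 points | 8.8 points |
| 20% | 8.0 points | 7.5 points |
| 30% | 7.0 points | 6.2 points |
| 40% | 6.0 points | 5.0 points |

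The odds ratio, which the logistic model estimates, moves the same way. Unadjusted, it is (0.35/0.65)/(0.25/0.75) = 1.62 for POD 1–5. At q = 20% with independent days it is (0.48/0.52)/(0.40/0.60) = 1.38.

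**4. Power.** With a larger assumed contrast of 40% against 20%, 55 per arm and two-sided α = 0.05, the normal approximation for two proportions gives 63% for POD 1–5 alone. Adding POD 0 with independent days gives 50% at q = 10%, 31% at q = 30% and 19% at q = 50%. With correlation 0.5 the last two are about 25% and 12%.

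**5. Insulin.** Total over POD 0–5 = POD 0 units + POD 1–5 units. If the POD 0 mean is the same in both arms, it cancels:

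E(control) − E(investigational) over POD 0–5 = the same difference over POD 1–5.

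POD 0 contributes only its variance and its covariance with later days. It widens the interval without pulling the mean difference toward zero.

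**The case against.** The strongest reply is that this is a design choice. The Outcomes section and Table 4 agree on POD 0–5, and both call the outcome postoperative. POD 0 comes after randomisation and after the first PN infusion, so comparing postoperative glycaemia between two strategies that begin on POD −1 is a coherent question. The protocol says only that the outcomes partly reflect carbohydrate load, which is a caveat and not a promise that the window tracks exposure. All this stands: there is no contradiction and no wrong figure. What it leaves unanswered is that pooling POD 0 under an *any* rule narrows the contrast, and the article gives no reason for the pooling.

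Three stronger readings are tempting and are not supported.

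- **Omitting POD −1 is an error that leaves 20% of PN unseen.** The share is right (80/400 = 20%), but POD −1 is preoperative and outside a postoperative outcome by definition. Glucose is monitored daily during the intervention period, and POD −1 glucose is compared between arms as a safety laboratory value, although its timing relative to the infusion is not stated.
- **The window biases the comparison.** POD 0 events equal in both arms reduce power and attenuate the POD 1–5 contrast; they cannot produce a false difference.
- **Insulin is diluted in the same way.** It is not, as step 5 of the working shows.

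It is also fair to say that POD 1–5 is not a clean window. The protocol places the catabolic peak in the first 48–72 hours after surgery, so stress hyperglycaemia may continue past POD 0. POD 1–5 would also miss any carry-over of POD −1 PN into POD 0.

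**Conclusion.** The point holds in a limited form. The exploratory hyperglycaemia outcome mixes a day without PN with five PN days, and the *any* rule turns POD 0 events common to both arms into dilution of the risk difference. The reduction is roughly the POD 0 event risk if days are independent, and more if they are positively correlated. Over assumed POD 0 risks of 10–40%, a 10-point difference becomes 9.0–6.0 points with independent days and 8.8–5.0 points with correlation 0.5.

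These sizes rest on assumed event rates, on equal POD 0 risk in the two arms and on the assumed correlation; none of these comes from the documents. Nor is a 10-point effect derived from the 6.2% glucose contrast. The consequence is lost power and a harder-to-read null result on an exploratory outcome. The primary endpoint, the two key secondary endpoints and the sample size are unaffected. Severity: minor.

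**What to change.** Keep POD 0–5 as the prespecified exploratory comparison. Replacing or demoting it during open-label recruitment would be harder to defend than adding to it. Before the coded labels are released, add to Table 4 and to the glycaemic paragraph under Outcomes a supplementary between-arm comparison over POD 1–5 of (a) any glucose ≥180 mg/dL and (b) total insulin, using the tests already named, and show POD 0 separately by arm. State that any remark on the formulations' carbohydrate load will rest on both windows. If the SAP, which is not shown, already has such an analysis, a pointer to it is enough.

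The cost is a wording change and one more exploratory analysis. Glucose is already monitored daily; insulin is already recorded for the POD 0–5 total and needs only to be kept by day. The downsides are one more exploratory estimate to report and the two limits of POD 1–5: it omits any POD −1 carry-over into POD 0, which the separate POD 0 display would still show, and it does not remove stress hyperglycaemia that persists after the day of surgery.

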### Randomization and allocation concealment

**Random sequence generation.** Eligible participants are randomly allocated in a 1:1 ratio. The master allocation sequence was generated in advance for 120 sequential allocations using a custom Python script, with a fixed seed and permuted blocks of variable size (4 and 6) in randomly chosen order. Stratified randomization is not used because the anticipated low proportion of total gastrectomy would produce imbalanced strata and incomplete blocks in the small stratum; extent of gastric resection and baseline nutritional status are instead controlled analytically through a prespecified covariate-adjusted (ANCOVA) analysis, and a subgroup analysis by extent of resection (total versus distal gastrectomy) is prespecified as exploratory in the Statistical analysis section.

**Allocation concealment.** The master sequence is held in read-only form by a single dedicated clinical research coordinator (CRC) in a password-protected directory inaccessible to any other member of the trial team. The CRC has no role in determining participant eligibility, enrolling or consenting participants, administering the assigned interventions, or assessing study outcomes, ensuring that knowledge of the allocation sequence cannot influence enrollment decisions or outcome assessment. File integrity is verified by a SHA-256 cryptographic checksum computed at the time of sequence generation and stored separately, providing an audit trail against post-hoc modification; allocation concealment per se is ensured by the procedural safeguards described in the Allocation procedure section.

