### Statistical analysis

**Analysis populations.** All efficacy analyses are performed in the intention-to-treat (ITT) population, comprising all randomized participants analyzed in the group to which they were allocated. The per-protocol population is defined as participants who completed the planned PN intervention through POD 5, received at least 90% of the planned cumulative allocated PN volume or amino acid dose, completed the POD 5 nitrogen balance assessment, and had no prespecified major protocol deviations; this population will be used for sensitivity analyses of the primary and key secondary outcomes. The safety population comprises all participants who received at least one administration of allocated PN.

**Primary analysis.** The primary outcome is compared between the investigational and control arms using a two-sample t-test, with the between-group mean difference reported with a 95% confidence interval; the Wilcoxon rank-sum test is used as a sensitivity analysis if distributional assumptions are clearly violated. In a prespecified adjusted analysis, POD 5 nitrogen balance is modelled by analysis of covariance (ANCOVA) with treatment arm as the factor and extent of gastric resection and baseline nutritional status as covariates.

**Mechanistic analyses of the primary endpoint.** To separate the arithmetic and metabolic components of the endpoint, prespecified mechanistic analyses compare between arms (a) total nitrogen intake, (b) urinary urea nitrogen excretion, and (c) net nitrogen retention on POD 5, and evaluate nitrogen-utilization efficiency (net retention relative to delivered nitrogen), and, in an exploratory analysis, adjust the primary endpoint for delivered nitrogen as a covariate. Because delivered nitrogen is a post-randomization variable largely determined by treatment allocation, adjustment for it cannot by itself causally separate nitrogen delivery from nitrogen utilization; these analyses are exploratory and descriptive, use already-recorded variables, and are reported with 95% confidence intervals as hypothesis-generating without causal claims. The partial dependence of nitrogen balance on nitrogen intake is acknowledged as a limitation that these analyses are designed to characterize.

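### Insulin requirement is compared without baseline diabetes in the analysis, although diabetes is recorded and the companion hyperglycaemia outcome adjusts for it: a valid test that gives up precision

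*Protocol article*

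**What the plan says.** The glycaemic-control block of Table 4 has two outcomes over the same window.

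- **Hyperglycaemia** (any glucose of 180 mg/dL or more) is reported by baseline diabetes status and analysed by "Chi-square or Fisher’s exact test; logistic regression adjusting for diabetes".
- **Insulin requirement**, defined as "Total insulin units administered during POD 0–5", is analysed by "Two-sample t-test or Wilcoxon rank-sum test". No covariate or stratum is named.

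The Outcomes section introduces both in one sentence, with hyperglycaemia "stratified by baseline diabetes status, together with the cumulative insulin requirement during the same period". The stratification there attaches to hyperglycaemia only.

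Elsewhere in the article:

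- Randomization and allocation concealment: "Stratified randomization is not used"; permuted blocks of 4 and 6 are used.
- Statistical analysis: the one prespecified ANCOVA concerns POD 5 nitrogen balance, with "extent of gastric resection and baseline nutritional status as covariates". Diabetes is not among them.
- Table 1: patients with diabetes can enter unless it is decompensated or HbA1c exceeds 9.0%.
- Statistical analysis: outcomes other than the primary and the two key secondary endpoints are exploratory and reported with 95% confidence intervals. Insulin requirement belongs to that group.

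**The concern.** By adjusting hyperglycaemia for diabetes, the sponsor treats diabetes as prognostic for perioperative glycaemia. The same reasoning applies at least as naturally to insulin dose, yet the next row leaves it out and gives no reason.

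Two things follow. First, the variation in insulin between participants with and without diabetes stays in the error term, so the confidence interval is wider than the recorded data require. Second, if one arm happens to hold more participants with diabetes, the insulin comparison will show it and the adjusted hyperglycaemia model will largely not. The two glycaemic results could then diverge because of case mix, and a reader could not tell this from an effect of the product.

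**Working it through.** **Inputs from the article.** 55 participants per arm, 1:1, unstratified. The figure reproduces: n = 2 × (1.960 + 0.842)² × 5² / 3² = 43.6, so 44 per arm, and 88 / 0.80 = 110. This calculation serves the primary outcome. The article states no power, SD or effect for insulin and no diabetes prevalence, so everything below on those is assumption.

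**1. How often will diabetes be imbalanced?** With prevalence p, treating the arms as independent binomials, the SD of the difference in proportions is √(2p(1 − p)/55). A difference of 10 points or more means at least 6 participants (6/55 = 10.9 points).

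| Assumed p | SD of difference | P(10 points or more) | P(15 points or more) |
|---|---|---|---|
| 10% | 5.7 points | 8% | 0.7% |
| 20% | 7.6 points | 19% | 4% |
| 30% | 8.7 points | 25% | 8% |

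**2. How much variance does adjustment remove?** Let B = p(1 − p)Δ², where Δ is the difference in mean insulin between participants with and without diabetes. Let W = p·V₁ + (1 − p)·V₀ be the variance within those groups. The unadjusted arm difference has variance 2(B + W)/55 and the adjusted one about 2W/55, so the proportion saved is B/(B + W).

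All cases below use p = 20%. In A and B, insulin is zero for non-users and gamma with shape 1.5 for users, so the variance is q·m²·(1 + 1/1.5) − (q·m)² for use probability q and mean m among users.

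- **A, moderate effect of diabetes** (80% use with mean 40, against 40% with mean 15): group means 32 and 6, Δ = 26. V₁ = 2133.3 − 1024 = 1109.3; V₀ = 150 − 36 = 114. B = 0.16 × 676 = 108.2; W = 221.9 + 91.2 = 313.1. Saving 108.2/421.2 = 26%.
- **B, strong effect** (90% use with mean 60, against 25% with mean 12): group means 54 and 3, Δ = 51. V₁ = 5400 − 2916 = 2484; V₀ = 60 − 9 = 51. B = 0.16 × 2601 = 416.2; W = 496.8 + 40.8 = 537.6. Saving 416.2/953.8 = 44%.
- **C, varying the spread** (mean 50 with diabetes; without it, 40% use with mean 10 and SD 10): Δ = 50 − 4 = 46, V₀ = 0.4 × 200 − 16 = 64, B = 0.16 × 2116 = 338.6. An SD of 25, 50 or 75 in diabetes gives W = 176.2, 551.2 or 1176.2, and a saving of 66%, 38% or 22%.

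Simulation of A and B at 10%, 20% and 30% prevalence (4,000 trials per scenario) gave variance ratios of about 1.3 to 1.9, that is savings of 1 − 1/1.3 = 23% to 1 − 1/1.9 = 47%. A lognormal version of C with SD 25 gave 63%. Roughly 20% to 60% is a fair summary.

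**3. Is the unadjusted test sound?** In the same simulations with no treatment effect, the t-test rejected in 4.2% to 5.6% of trials and the Wilcoxon test in 4.2% to 5.7%. The mean estimate was zero within simulation error.

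**4. What happens once an imbalance has occurred?** Six extra participants with diabetes in one arm shift the expected difference by (6/55)Δ. That is 2.8 units in A, against a standard error of √(2 × 421.2/55) = 3.9, and 5.6 units in B, against √(2 × 953.8/55) = 5.9. Among simulated null trials with an imbalance of 10 points or more, the false-positive rate was 10% to 28% (t-test) and 9% to 22% (Wilcoxon), against 3% to 6% with diabetes in the model.

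**The case against.** **The stated tests are valid, and chance imbalance is already in their standard error.** This stands. A reader might infer that imbalance biases the comparison or inflates its error rate. Step 3 shows otherwise; the raised rates in step 4 come from looking only at trials already known to be imbalanced.

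**The outcome is exploratory.** This also stands. The primary endpoint, the Holm family and the sample size are untouched. However, exploratory outcomes are to be reported as estimates with confidence intervals, for which precision matters, and the plan already adjusts another exploratory outcome, postoperative complications.

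**The two rows differ less than they seem.** The hyperglycaemia row also names an unadjusted test first, with the logistic model beside it, and most other exploratory outcomes are compared without covariates. So the rows do not rest on opposed principles; the insulin row lacks an adjusted analysis that its neighbour has.

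**The SAP may supply it.** It is not shown, and it may. But the article presents Table 4 as holding the prespecified analyses of the secondary outcomes, and Table 4 names a method for this one. If SAP v1.0 adjusts for diabetes, the table should agree with it.

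**Stronger claims the article does not support.** It nowhere calls diabetes the dominant predictor of insulin dose or quantifies its effect. Nor does it support a large power gain, which needs an assumed treatment effect. Glucose delivery at 20 kcal/kg is 20 × 70.7/0.69 = 2,049 mg/kg for control and 20 × 64.4/0.67 = 1,922 mg/kg for the investigational product, about 6% less. Insulin need not follow in proportion, but nothing in the article justifies assuming a large reduction.

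**Conclusion.** The point holds as a minor, free improvement. Table 4 fixes an unadjusted comparison for insulin requirement while a recorded baseline variable, already used for the companion outcome, is left out and is not balanced by the randomisation. The analysis is valid but less precise than it could be, and awkward to interpret if diabetes is imbalanced.

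The imbalance probabilities (8% to 25% for 10 points or more) depend only on 55 per arm and the assumed prevalence of 10% to 30%. The variance saving of roughly 20% to 60% depends on assumed insulin distributions and would be smaller if diabetes separated the groups less than in the cases above. No confirmatory conclusion of the trial depends on this row.

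**What to change.** In the insulin row of Table 4, name one analysis: a linear model for total insulin units over POD 0–5 with arm and baseline diabetes status, robust standard errors, and the mean difference with its 95% CI. Because the covariate is a baseline one and the model is linear, the target remains the difference in mean units between arms. Name the van Elteren test stratified by diabetes as a sensitivity analysis, to be run whatever the shape of the data; it targets a different quantity, so it should not replace the model after skewness has been inspected. Report descriptive results by diabetes status, as for hyperglycaemia. If SAP v1.0 is silent or repeats Table 4, amend it to match; if it already specifies such a model, only the table needs aligning.

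The cost is one degree of freedom and a few lines of text. No new data are needed. The trial is still recruiting and the article reports no between-group analysis before SAP v1.0, so a dated change made before the coded labels are released counts as prespecified. The same change made after an imbalance had been seen would not.
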